# Effect of acupuncture for patients with knee osteoarthritis: study protocol for a double-dummy randomized controlled trial

**DOI:** 10.1186/s13018-023-04198-2

**Published:** 2023-10-17

**Keywords:** Knee osteoarthritis, Acupuncture, Pain, Randomized controlled trial

## Abstract

**Background:**

Acupuncture has been used to relieve chronic pain in patients with knee osteoarthritis (KOA), but the evidence is contradictory. Therefore, we carefully designed a double-dummy randomized controlled trial (RCT) to explore the therapeutic effect of acupuncture for KOA.

**Methods/design:**

A total of 138 eligible participants with KOA who consent to participate will be randomly divided into Groups A, B, and C in a ratio of 1:1:1. Participants in Group A will receive verum acupuncture and placebo gel, while those in Groups B and C will be treated with diclofenac diethylammon gel and sham acupuncture, sham acupuncture and placebo gel, respectively. The patients will receive 4 weeks of treatment, five times a week, including acupuncture treatment once a day for 30 min and gel treatment three times a day. The primary outcome will be the change of Western Ontario and McMaster Universities Osteoarthritis Index (WOMAC) at week 4. The secondary outcomes will include visual analog scale (VAS), Arthritis Quality of Life Measurement Scale Simplified Scale (AIMS2-SF), Beck Anxiety Inventory (BAI), Beck Depression Inventory (BDI) and Credibility/Expectancy Questionnaire. The evaluation will be performed at baseline, week 4, 8, and 12 after randomization.

**Discussion:**

This double-dummy RCT used diclofenac diethylammon gel as a positive control, and the completion of this trial will provide detailed and accurate evidence of the efficacy and safety of acupuncture for KOA.

*Trial registration*: China Clinical Trials Registry No.ChiCTR2100043947. Registered on September 24, 2020. https://www.chictr.org.cn/showproj.html?proj=122536.

## Introduction

Knee osteoarthritis (KOA) is a common degenerative disease of the knee joint, which is characterized by subchondral bone sclerosis, articular cartilage degeneration, periarticular bone hyperplasia, synovial lesions, and joint capsule contracture [1]. However, the precise etiology of KOA remains unclear, which may be related to obesity, gut microbiome [2], local musculoskeletal injury of knee joint [3], and so on. An epidemiological survey shows that in the USA, about 240 people per 100,000 people are diagnosed with KOA each year [4]. The prevalence of KOA in Italy, Greece, and Spain was 5.4%, 6.0%, and 12.2%, respectively [5]. The KOA is not only detrimental to the physical function of the patients and their quality of life, but also creates a huge economic burden for society as well [6, 7]. This degenerative disease will gradually worsen with age, and now, KOA has become one of the major health risks for middle-aged and elderly individuals [8].

Patients suffering from KOA are usually limited in their daily activities due to intermittent pain, weight-bearing pain, joint stiffness, and limited mobility. Patients with KOA suffer from knee pain that negatively affects their quality of life, which is one of the main reasons for them to seek medical treatment [9]. Currently, the treatment of KOA aims to relieve pain and improve knee function, so as to improve the patient's quality of life [10]. At present, there are many clinical treatments for KOA, including drug, physiotherapy, lifestyle modifications and other conservative treatments, as well as surgical treatment. However, drug treatment usually has some side effects and gastrointestinal adverse reactions [11], and the surgical treatment is expensive and frequently associated with contraindications and complications, which limit its wide application [12]. Therefore, more and more KOA patients tend to choose complementary and alternative treatment, such as manual therapy [13], acupuncture, and physical exercise [14].

Since ancient Chinese times, acupuncture has been used as a complementary and alternative treatment for KOA [15, 16]. Systematic reviews of randomized controlled trials (RCTs) have shown that acupuncture is indeed beneficial for KOA [15, 17]. In addition, studies have shown that acupuncture is more effective in treating KOA than other physical therapies such as pulsed electrical stimulation, aerobic exercise, and muscle strengthening exercise [18]. However, some guidelines stated that there was insufficient evidence to recommend acupuncture for KOA patients [19, 20]. Additionally, some research reports show that although patients report less pain, the improvement in verum acupuncture over sham acupuncture is not clinically significant [21, 22]. So, we decided to conduct an RCT to explore whether acupuncture is beneficial to KOA patients.

Topical non-steroidal anti-inflammatory drugs (NSAIDs) are another method for clinical treatment of KOA. Current management guidelines recommend topical NSAIDs as first-line therapy for KOA, especially in elderly patients [19, 23]. Topical NSAIDs are nearly as effective as oral NSAIDs in analgesia, improving physical function, and reducing stiffness, with fewer systemic adverse reactions [24, 25]. Moreover, clinical RCTs have also demonstrated the efficacy of diclofenac diethylammon gel in the treatment of KOA [26–28]. Therefore, we carefully designed this double-dummy RCT and used diclofenac diethylammon gel as a positive control, to explore the therapeutic effect of acupuncture for KOA patients.

## Methods and analysis

### Study design

This is a double-dummy RCT that aims to compare the analgesic efficacy of acupuncture, diclofenac diethylammon, and placebo in the treatment of KOA, which will conduct research and write research reports in accordance with the CONSORT recommendations for reporting randomized trials. Based on clinical criteria developed by the American College of Rheumatology (ACR) [29], 138 patients with KOA will be recruited. The ratio of 1:1:1 will be used to randomize all patients after informed consent is obtained, which are Group A: verum acupuncture group (verum acupuncture and placebo gel; verum acupuncture is traditional acupuncture, a technique for treating diseases by stimulating acupoints with acupuncture); Group B: diclofenac diethylammon group (diclofenac diethylammon gel and sham acupuncture; sham acupuncture is placebo acupuncture); and Group C: placebo group (sham acupuncture and placebo gel) to receive treatments. There will be 20 sessions of treatment in total between weeks 1 and 4, with follow-ups at weeks 8 and 12. Figure 1 shows the flowchart of the trial process, and Table 1 shows the enrollment, treatment, and assessment schedule (Fig. 1 and Table 1).

**Fig. 1 Fig1:**
[figure not shown]
Flowchart of the trial

**Table 1 Tab1:** Study design schedule

Time point (week)	Baseline		Treatment phase			Follow-up	
	0-week	1-week	2-week	3-week	4-week	8-week	12-week
*Enrollment*							
Eligibility screen	×						
Informed consent	×						
Allocation	×						
Randomization	×						
*Interventions*							
Group A (*n* = 46)		×	×	×	×		
Group B (*n* = 46)		×	×	×	×		
Group C (*n* = 46)		×	×	×	×		
*Assessments*							
WOMAC	×				×	×	×
VAS	×				×	×	×
AIMS2-SF	×				×	×	×
BAI	×				×	×	×
BDI	×				×	×	×
Expectancy questionnaire	×						
*Participants safety*							
Adverse events	×	×	×	×	×	×	×

Qualification screening and informed consent will be completed before the assignment. After allocation, each patient will be treated within 4 weeks. The evaluation will be performed at baseline and weeks 4, 8, and 12, respectively, after randomization. Adverse events will be recorded on the case report form at any time during treatment

### Study setting and recruitment

The trial will be conducted at the First Affiliated Hospital of Henan University of Chinese Medicine. The outpatient department of the hospital will recruit 138 KOA participants. The clinical research coordinator will perform a preliminary screening of participants and provide a detailed explanation to eligible participants in detail of the purpose of the study, and written informed consent will be obtained [30]. Afterward, the clinical assessor will conduct baseline assessments of participants who have obtained written informed consent. A randomization number will be assigned to each patient at enrollment, which is a unique direct identifier included on the case report forms (CRF).

### Participants

It is required that all participants sign the informed consent document before inclusion in this trial, which outlines the trial's benefits and risks. Moreover, patients can withdraw from the study at any time without penalty or loss of benefits and without any reasons. This trial is a voluntary one, it is the patient's right to decide whether to participate in this trial, and all information about the participants will be kept confidential.

### Inclusion criteria

The inclusion criteria are as follows: (1) adults aged 45–75 years, including the age of 45 and 75, male or female; (2)patients must fulfill the standard diagnosis of KOA established by the ACR; (3) radiologic confirmation of KOA [31] (Kellgren–Lawrence grades I to III); (4) VAS score ≥ 40 mm; (5) symptoms of knee bone friction sound during activity, pain, and morning stiffness ≤ 30 min have been present for over 6 months; and (6) participants fully understand this trial and written informed consent is signed.

### Exclusion criteria

The exclusion criteria are as follows: (1) patients with knee infection; (2) patients with any ligament or meniscus tear or acute inflammation of the synovial sac; (3) patients with a history of local tumor or malignancy of the knee joint; (4) patients with physical or laboratory findings of the presence of infection, autoimmune diseases, or inflammatory arthritis; (5) patients who have received hyaluronic acid injections or corticosteroid injections within the last 3 months; (6) patients who received acupuncture or electro-acupuncture within 8 weeks prior to participating in this trial; and (7) patients suffering from pain in other body parts.

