### Randomization

In this trial, an independent researcher, who will not involve in any other trial procedures, will use a computer to create a random number list and then randomly assign eligible patients in a 1:1:1 ratio to one of the three groups. Sealable envelopes will be used for randomization allocation. The evaluator will inform the acupuncturists after the participant signs the informed consent form and completes the baseline assessments. The acupuncturists will open the envelope according to the participant’s screening sequence number and assign them to different groups to receive the intervention.

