### Blinding

Acupuncturists cannot be blinded as they will be required to apply the various stimulation methods to intervene. However, there will be blinded of group assignments among the participants, because the acupuncture needles are the same, and the diclofenac diethylammon gel and placebo gel are identical in appearance. In addition, participants will be arranged in different rooms for treatment, in order to prevent them from communicating with each other to understand their treatment programs, and the acupuncturists will not communicate any information to participants about their treatment programs. Group assignments will be concealed from outcome assessor and data analysts. Only after data analysis, we will perform unblinding analysis. In the data summary stage, the three separation principles of researcher, operator, and statisticians will be implemented.

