### Safety assessment

During the trial, adverse events (AEs) will be documented by using safety assessments, which include date, extent, frequency, and duration of AEs. The most common AEs related to acupuncture in this trial were pain, bleeding, hematomas, fainting, or other severe events. Moreover, redness, swelling, and itching of the skin are the AEs associated with diclofenac diethylammon gel. In the event of adverse events, emergency measures will be taken and documented in detail in the CRF. In the event of severe adverse events, the research ethics committee will determine whether the participant should be withdrawn from the study. Patients may withdraw from this trial if any AEs occur.

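### The printed eligibility list has no exclusion for known hypersensitivity to diclofenac, other NSAIDs or the gel, or for damaged knee skin, although one third of patients are randomised to blinded diclofenac gel

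*Protocol article*

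**What the plan says.** The Inclusion criteria section has six numbered items: age, ACR diagnosis, radiographic grade, VAS pain, symptom duration, and understanding with signed consent. The Exclusion criteria section has seven. It begins "The exclusion criteria are as follows: (1) patients with knee infection" and closes with "and (7) patients suffering from pain in other body parts". The items between cover ligament, meniscus or acute synovial problems; local tumour; infection, autoimmune or inflammatory arthritis findings; knee injections in the last 3 months; and acupuncture in the last 8 weeks.

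Under Group B, diclofenac gel goes on each affected knee three times a day, five days a week, for four weeks. The Blinding section says that "the diclofenac diethylammon gel and placebo gel are identical in appearance". The Safety assessment section states that "redness, swelling, and itching of the skin are the AEs associated with diclofenac diethylammon gel", and lists bleeding and hematomas among the acupuncture events.

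Three provisions act before treatment. In Study setting and recruitment, "The clinical research coordinator will perform a preliminary screening of participants". In Participants, "It is required that all participants sign the informed consent document before inclusion in this trial", and that document sets out benefits and risks. In Randomization, "The evaluator will inform the acupuncturists after the participant signs the informed consent form and completes the baseline assessments"; the acupuncturists then open the envelope.

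**The concern.** A trial that assigns a drug by chance normally bars patients already known not to tolerate it. Here the protocol names skin reactions as the harms of the gel, yet no eligibility item asks about a past reaction to diclofenac or another NSAID, or about the state of the skin where the gel is applied and the needles go in. The arm is unknown at screening, so only a rule applied to every entrant can keep such a patient from the active gel. What is at stake is participant safety: a risk that can be checked beforehand is left to individual judgement.

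**Working it through.** The plan gives no figure on this point. The check is a reading of the criteria, followed by simple exposure arithmetic.

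**Step 1: count and read the criteria.** 6 inclusion + 7 exclusion = 13. Items on hypersensitivity to diclofenac, NSAIDs or the gel: 0 of 13. Items on non-intact or diseased, uninfected knee skin: 0 of 13. Items on a bleeding disorder or anticoagulation: 0 of 13.

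**Step 2: set the nearest items beside the named harms.**

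| Provision | What it removes or does | What it leaves |
|---|---|---|
| Exclusion 1 | Knee infection | Allergy; uninfected skin damage |
| Exclusion 3 | Local tumour or malignancy of the knee | Same |
| Exclusion 4 | Infection, autoimmune disease, inflammatory arthritis | Same |
| Discontinuation criterion 4 | Stops a participant after a serious event | Acts only after exposure |
| Safety assessment | Emergency measures, ethics committee review, withdrawal | Acts only after exposure |

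**Step 3: look for a check before allocation.** The coordinator's screening has no stated criterion for these risks. Consent informs the patient but is not an eligibility rule. The acupuncturists come in after consent and baseline assessment, so their judgement is not described as a step before allocation.

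**Step 4: exposure.** Share allocated diclofenac gel: 46/138 = 1/3. Applications per affected knee: 3 per day × 5 days × 4 weeks = 60. These figures describe every patient in the arm, not patients with a contraindication.

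**Step 5: illustration only.** The documents give no prevalence. Let p be an assumed share of randomised patients with such a contraindication. In an arm of 46, the expected number is 46p and the chance of at least one is 1 − (1 − p)^46:

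| Assumed p | Expected number | Chance of at least one |
|---|---|---|
| 1% | 0.46 | 37% |
| 2% | 0.92 | 61% |
| 5% | 2.3 | 91% |
| 10% | 4.6 | 99% |

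The table shows how the answer depends on p. It is not evidence that any patient is affected.

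**The case against.** The strongest reply is that the contraindications come from clinical reasoning, not from the document. The Safety assessment section lists events to record. An expected local reaction is not in itself a contraindication, and that section does not contradict the exclusion list. This stands, and it limits the weight of the point.

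Second, several safeguards exist. Consent outlines risks and comes before allocation, so a patient who knows of an allergy can decline. Inclusion criterion 6 requires full understanding of the trial. Exclusion 4 refers to physical findings, so visibly diseased skin might be noticed. The Introduction credits topical NSAIDs with "reducing stiffness, with fewer systemic adverse reactions". All of this lowers the risk, but none of it is a rule against these patients, and fewer systemic reactions does not mean no local ones.

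Third, an article condenses the full protocol. That defence is only partial, because the list is printed as closed, with exact time windows and no pointer to further criteria.

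A reader might infer that nothing in the criteria keeps out patients unsuited to needling. The document does not support that: exclusions 1, 3 and 4 remove some of them. A reader might also treat bleeding risk as an equal gap. It is weaker. Groups B and C (92 of 138) are needled at 1–2 mm without manipulation; only Group A (46) has 21–26 mm with manipulation, and a sensible rule there would largely write down clinical discretion.

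**Conclusion.** The point holds in a narrow form. Followed as written, the criteria leave a patient with a known NSAID allergy or with broken or diseased, uninfected knee skin eligible for a 1-in-3 allocation to blinded diclofenac gel. The conclusion rests on two assumptions: that the printed list is complete, and that known hypersensitivity or damaged skin is a reason not to apply the gel, which is clinical inference from the named harms. The number of patients affected cannot be stated. A reader might infer a threat to the treatment estimate or to power; nothing in the document supports that, and none is claimed. This is a minor safety improvement, not a flaw in the trial's validity.

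**What to change.** Add one item to the Exclusion criteria, applied to all entrants before randomisation: *known hypersensitivity or other contraindication to diclofenac, other NSAIDs or the gel, or non-intact or diseased skin at the application or needling site*. It can be checked by history and inspection at the existing screening.

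Optionally, add a bleeding disorder or anticoagulation that the investigator judges unsuitable for needling at 21–26 mm, without barring every anticoagulant user.

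The cost is a few screen failures, whose number is unknown because no prevalence is given. Timing matters too. The Trial status section says recruitment had not begun but plans it from October 1, 2023, 16 days before the publication date of October 17, 2023. If recruitment has started, the change needs an amendment and protects only later entrants.

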### Discontinuation criteria and modification

Participants who meet the following criteria will be excluded from the trial during the trial period: (1) receiving additional treatments that may interfere with acupuncture's efficacy, violating the protocol, such as taking analgesics without permission or receiving other treatments; (2) participants were reluctant to continue treatments; (3) missing more than 4 of 20 acupuncture treatment sessions; and (4) serious adverse events occurred and doctors consider the trial should be terminated.

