### Interventions

This trial is divided into three groups: Group A: verum acupuncture group (verum acupuncture and placebo gel), Group B: diclofenac diethylammon group (diclofenac diethylammon and sham acupuncture), and Group C: placebo group (sham acupuncture and placebo gel). Aside from the experimental scheme, patients will be advised not to use other any methods for the treatment of KOA. At the beginning of the trial, all licensed acupuncturists, who have at least 6 years of experience in acupuncture, will be trained in the clinical operation organized by the research group.

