### Statistical analysis

The statistical analysis procedure of this trial will be performed using SPSS 22.0 software (IBM Corporation, Armonk, NY, USA). Statisticians responsible for data analysis will be independent of the research team and blind to the test settings. The data will be tested for normality using the quantile–quantile plots. We will analyze the data from WOMAC, VAS, AIMS2-SF, BAI, and BDI within the group and use paired-sample t-tests for those data that follow normal distributions, and in the case of data that did not conform to the normal distribution, Wilcoxon test will be used. Age, height, weight, and outcome assessments will be compared among the three groups, the one-way analysis of variance (ANOVA) will be applied to data conforming to a normal distribution, and the Kruskal–Wallis one-way ANOVA will be used to analyze data that do not follow a normal distribution. Intention-to-treat analysis will be used for outcome measurements to analyze missing values, based on the last observation carried forward method. In the analysis of missing values, only patients who attended at least 80% of the sessions and completed the follow-up in the allocated intervention group will be included. In addition, data will be tested by bilateral tests, and the confidence intervals are all 95% bilateral; *p* < 0.05 (*α* = 0.05) is considered to indicate statistical significance.

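### The exclusion for taking other treatment is not limited to weeks 1–4, so follow-up scores may be replaced or dropped and maintenance of benefit at weeks 8 and 12 may be overstated

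*Protocol article*

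**What the plan says.** All references are to the protocol article.

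- **Discontinuation criteria and modification:** "Participants who meet the following criteria will be excluded from the trial during the trial period: (1) receiving additional treatments". The examples given are "such as taking analgesics without permission or receiving other treatments". The participant is excluded from the trial, not merely from study treatment, and the period is not defined.
- **Study design:** "There will be 20 sessions of treatment in total between weeks 1 and 4, with follow-ups at weeks 8 and 12". Table 1 separates a treatment phase from a follow-up phase, and its note adds: "The evaluation will be performed at baseline and weeks 4, 8, and 12, respectively, after randomization".
- **Interventions:** "patients will be advised not to use other any methods for the treatment of KOA". No end date is given.
- **Statistical analysis:** "Intention-to-treat analysis will be used for outcome measurements to analyze missing values, based on the last observation carried forward method". The next sentence restricts an analysis of missing values so that "only patients who attended at least 80% of the sessions and completed the follow-up in the allocated intervention group will be included".

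Nowhere does the article say that an excluded participant continues to be assessed.

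**The concern.** Eight weeks without study treatment lie between the end of treatment and the last visit (12 − 4 = 8). Participants enter with a VAS of at least 40 mm and more than six months of symptoms, so some may turn to other treatment in that time. Those who do so are plausibly the ones whose pain has returned. If they are then excluded, whether a follow-up score exists depends on the outcome that the score would have measured.

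Neither stated way of handling the gap repairs this. Carrying the last score forward can place an end-of-treatment result in an off-treatment visit. The completer wording removes the participant. Removing randomised participants for what they did after randomisation also sits badly with an analysis called intention-to-treat. At stake is what the secondary results at weeks 8 and 12 say about whether benefit lasts.

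**Working it through.** **1. What happens to a participant excluded after week 4, on the plain reading**

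| Time of exclusion | Week 8, carried forward | Week 12, carried forward | Completer wording |
|---|---|---|---|
| Between weeks 4 and 8 | week-4 score | week-4 score | left out |
| Between weeks 8 and 12 | observed | week-8 score | left out |

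Only the first row moves an end-of-treatment score into follow-up. In the second row the carried score is already off treatment.

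**2. Inputs.** The Sample size section gives WOMAC total reductions of 17 (A), 13 (B) and 10 (C), SD 10.24 and two-sided α = 0.05. A three-group one-way ANOVA F test on these figures needs 42 per group (power 0.8003), which matches the plan. The article gives no rate of other treatment after week 4, so every exclusion share below is an assumption. The plan's 10% is loss from any cause.

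**3. Simple illustration.** Let d be the planned week-4 change and p the share excluded before week 8. Assume that those excluded truly return to a change of 0 and all others keep d.

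- True mean at follow-up = (1 − p) × d
- Mean with week 4 carried forward = d
- Overstatement within an arm = p × d
- Bias in the A–C difference = 17 × p(A) − 10 × p(C)

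With p = 10% in both arms:

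- A: true 0.9 × 17 = 15.3, reported 17, overstated by 1.7
- C: true 0.9 × 10 = 9.0, reported 10, overstated by 1.0
- A–C: true 15.3 − 9.0 = 6.3, reported 7.0, overstated by 0.7

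The sign of the A–C bias depends on the shares:

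- 20% in A and 10% in C: 3.4 − 1.0 = +2.4
- 10% in A and 30% in C: 1.7 − 3.0 = −1.3

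**4. A less restrictive model, by simulation.** Assumptions: normal scores with the planned means and SD, week-4/week-12 correlation 0.5, and exclusion of the 10%, 20% or 30% of each arm with the greatest loss since week 4. The week-4 score is carried forward. Group A results, in points of reduction:

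| True retained benefit | Method | 10% | 20% | 30% |
|---|---|---|---|---|
| 0 | carried forward | 3.5 | 6.3 | 8.7 |
| 0 | completers | 1.0 | 1.8 | 2.5 |
| 8.5 | carried forward | 11.2 | 13.1 | 14.6 |
| 8.5 | completers | 9.5 | 10.3 | 11.0 |

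Both methods overstate the within-arm benefit, completers less so. With 20% excluded per arm, the A–C difference under carry-forward goes from 0 to 1.4, or from 3.5 to 4.2. Among completers with equal shares it does not change.

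**The case against.** **The window may be narrower.** The trial period is undefined. Two of the four criteria concern unwillingness to continue treatment and missed sessions, and criterion (1) speaks of interference with acupuncture's efficacy, so the authors may have meant weeks 1–4 only. This stands as a doubt about intent. But the text does not say so, the criterion on serious adverse events has no such limit, and Table 1 records adverse events to week 12. That assessment stops is likewise inferred from exclusion from the trial.

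**The trigger is other treatment, not relapse.** A reader might infer that relapsing patients are removed as such. The article does not support that: a participant who worsens and takes nothing stays in and is measured, and the reference to permission implies that some analgesic use may be allowed. The link to relapse is plausible but not stated.

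**The sizes are assumed.** This stands. The simple model gives the same figures for carry-forward and completers only because it assumes that the others lose nothing and that exclusion is unrelated to the week-4 score. The simulation shows that the two methods differ.

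**Only secondary results are touched.** This also stands. The Secondary outcomes section lists total WOMAC at weeks 4 and 8, so the illustration in total points bears most directly on week 8. The WOMAC subscales, VAS, AIMS2-SF, BAI and BDI run to week 12.

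**Observed scores are not clean either.** Scores taken after other treatment has started include some of its effect. This is a real cost and the reason for a sensitivity analysis.

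**Conclusion.** The point holds as a conflict between stated rules. Read plainly, criterion (1) reaches into follow-up, and the missing-data wording then replaces or drops the scores concerned. If those who take other treatment are mainly those who worsened, maintenance of benefit within each arm is overstated in the week-8 and week-12 results. The size is unknown; 1.7 points in A and 1.0 in C at 10% excluded is an illustration resting on the assumptions in step 3.

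Two stronger conclusions are not supported. One is that acupuncture's advantage over placebo is inflated: the direction of the between-arm bias depends on how use of other treatment differs by arm, and the article gives nothing on that. The other is that the main result is at risk: the primary outcome is at week 4, and neither it nor the sample size is affected by exclusions after week 4.

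The matter cannot simply be left to an analysis plan, because scores that were never collected at weeks 8 and 12 cannot be recovered later.

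**What to change.** Reconcile the Discontinuation criteria and Statistical analysis sections so that meeting criterion (1) after week 4 does not end outcome assessment:

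- Record the date and type of any other KOA treatment, and complete the scheduled week-8 and week-12 assessments.
- Do not carry week-4 scores into those visits.
- Analyse the observed scores of all randomised participants, for example with a mixed model for repeated measures.
- Add a sensitivity analysis that treats other KOA treatment started after week 4 as loss of benefit.

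Advice to patients on other treatments is left to the investigators; only assessment and analysis change.

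The cost is a wording change, one case report form line at two visits already planned, and one extra analysis. The sample size does not change. The downside is that observed follow-up scores will include some effect of the other treatment, and the follow-up results may look less favourable.
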